### Criteria for Statistical Significance

The overall significance level will be set at .05. A Bonferroni correction will be applied, due to the similarity of the two proposed hypotheses, which means that each of the two primary hypotheses will be tested at a significance level of *P*=.025. Secondary analyses will be regarded as exploratory and will therefore not be tested for statistical significance, but the precision will be reported by 95% CI. They may influence the interpretation of findings of the primary analyses.

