### Statistical Power

The power calculations are based on, inter alia, the following assumptions:

In total, 20% of the participants were hypertensive at baseline [16].In total, 15.68% (1830/11,670) participants performed heavy occupational lifting at baseline (Table 2).In total, 55% of the participants who were normotensive at examination n would meet the case criteria (antihypertensive drug usage or an above median delta of SBP) at examination n+1.The intraperson correlation coefficient equals .5 in the cross-sectional analysis and .1 in the prospective analysis.

Table 5 shows the expected numbers of observations, participants, and “cases” that will be included in the primary analyses. It also shows the variance inflation factor, which is a function of the assumed intraperson correlation and the mean numbers of observations per participant.

**Table 5 table5:** Number of observations, participants, and estimated cases that we expect to include in the primary analyses.

Analysis	Number of observations	Number of participants	Observations/Participants	Estimated number of cases^a^	Variance inflation factor
Cross-sectional	11,670	7166	1.63	2334	1.31
Prospective	4746	3271	1.45	2610	1.05

^a^A case in the primary analysis will be defined as the shift from no use of antihypertensive drugs in examination n to use of antihypertensive drugs in examination n+1 or an above median delta value of systolic blood pressure (systolic blood pressure in examination n+1-systolic blood pressure in examination n).

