**Figure 2 figure2:**
[figure not shown]
Statistical power of detecting an association between heavy occupational lifting at examination n and antihypertensive drug usage or an above median delta of systolic blood pressure (SBP) at examination n+1, as a function of the underlying odds ratio between exposed and unexposed participants in the target population.

The statistical powers of the primary hypotheses are given in Figures 1 and 2. The calculations are based on the above assumptions, the propagation of error formulas, the central limit theorem, and a two-tailed significance level at *P*=.025, for each of the two hypotheses.

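### Holm's step-down would keep the plan's .05 familywise error and add some power for the second primary hypothesis; the fixed Bonferroni split is valid, so this is a cheap improvement, not an error

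*Protocol article*

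**What the plan says.** Under Criteria for Statistical Significance, the protocol article states: "The overall significance level will be set at .05". It then gives the method, "A Bonferroni correction will be applied, due to the similarity of the two proposed hypotheses", and the consequence: "each of the two primary hypotheses will be tested at a significance level of" .025. Secondary analyses are exploratory and are not tested.

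The Statistical Power section uses the same level. The text after Figure 2 refers to "the central limit theorem, and a two-tailed significance level at" .025 for each hypothesis. Method, level and power basis therefore agree.

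Three other places bear on the choice:

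- Primary Statistical Analyses presents the primary ORs with 95% intervals, not 97.5% intervals.
- Methodological Challenges says that a plain hypertension outcome would have left the prospective analysis underpowered, and that the case definition was widened for that reason.
- Flow of Participants says that the blood pressure and drug-use information will arrive after the protocol paper is submitted.

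**The concern.** Single-step Bonferroni holds each test at .025 whatever the other test shows. Holm tests the smaller P at .025 and, if that is rejected, the larger at .05. It keeps the familywise error at .05 under any dependence, which matters because the two analyses share participants and blood pressure readings. It rejects everything that Bonferroni rejects, and sometimes more.

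At stake is one outcome pattern: one primary hypothesis is rejected at .025 and the other has .025 < P ≤ .05. The present rule must leave the second unproven, although the same overall error rate would allow its rejection. The prospective test has the lower power at a common OR and gains more. It is also the analysis in which the authors were concerned about power.

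**Working it through.** **The plan's own figures.** The split is .05/2 = .025, as stated. The Table 5 variance inflation factors (VIF) follow from 1 + (m − 1)ρ:

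- cross-sectional: 1 + (11,670/7166 − 1) × 0.5 = 1.314 (stated 1.31);
- prospective: 1 + (4746/3271 − 1) × 0.1 = 1.045 (stated 1.05).

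The expected cases also reproduce: 11,670 × 0.20 = 2334 and 4746 × 0.55 = 2610. Figures 1 and 2 are not shown in the text at hand, so no stated power value could be checked.

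**Inputs.** From Statistical Power: "15.68% (1830/11,670) participants performed heavy occupational lifting at baseline", "20% of the participants were hypertensive at baseline" and "55% of the participants who were normotensive at examination n would meet the case criteria". From Table 5: the observations and VIFs above. Assumed, because the article does not give them: the true OR (taken as equal in both analyses) and the correlation between the two test statistics (0 to 0.3). The 20% and 55% are taken as the case shares p0 among the unexposed.

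**Single-test power.** SE(log OR) = √{VIF × [1/(n1 p1 q1) + 1/(n0 p0 q0)]}, with n1 exposed and n0 unexposed observations, q = 1 − p, and p1 obtained from p0 and the OR. The two-sided critical values are 2.241 at .025 and 1.960 at .05. At OR 1.25, log OR = 0.2231:

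| Analysis | n1 / n0 | p0 / p1 | SE | log OR / SE | Power at .025 | Power at .05 |
|---|---|---|---|---|---|---|
| Cross-sectional | 1830 / 9840 | .200 / .238 | .0691 | 3.23 | 83.8% | 89.8% |
| Prospective | 744 / 4002 | .550 / .604 | .0834 | 2.67 | 66.8% | 76.3% |

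**Holm, independent tests.** Power under Holm = power at .025 + (power at .05 − power at .025) × power of the other test at .025.

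- Prospective: .668 + (.763 − .668) × .838 = .747.
- Cross-sectional: .838 + (.898 − .838) × .668 = .878.

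**With correlation 0 to 0.3** (simulated bivariate normal test statistics, OR 1.25 in both):

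| Result | Bonferroni | Holm |
|---|---|---|
| Prospective rejected | 67% | 74-75% |
| Cross-sectional rejected | 84% | 87-88% |
| Both rejected | 56-59% | 68-70% |
| At least one rejected | 92-95% | 92-95% (identical at each correlation) |

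At OR 1.2 in both, prospective power rises from 48% to 55%. At OR 1.4 in both, it rises only from 96% to 98%. Reading the 20% and 55% as shares of the whole sample changes little: at OR 1.25, cross-sectional power goes from 83% to 86-87% and prospective power from 67% to 75%.

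**Only one association real.** With the other hypothesis null, the gain is at most (power at .05 − power at .025) × .025 if the tests are independent. At OR 1.2, cross-sectionally, this is (.743 − .645) × .025 = .0025, or about 0.3 points or less.

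**Error rates.** With both nulls true, the familywise error is the same under either rule: about 4.9% at correlation 0 and 4.8% at 0.3. With a cross-sectional OR of 1.25 and a null prospective association, the chance of a false prospective claim rises from 2.5% to about .025 + .025 × .838 = 4.6%.

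**Smaller prospective sample.** The abstract and Flow of Participants expect fewer than 1850 prospective participants, against 3271 in Table 5. With 1850 participants at an assumed 1.45 observations each (about 2683 observations), prospective power at OR 1.25 is about 41% under Bonferroni and 50% under Holm.

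**The case against.** The strongest reply is that nothing here is wrong. Bonferroni is valid under any dependence, was fixed in advance, and matches the level behind the power curves. That stands in full. A reader might infer that the plan miscontrols its error rate or misstates a figure. The article does not support that: the .025 reproduces exactly and the two sections agree.

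A reader might also infer that the plan throws power away for nothing. That goes too far, for three reasons, all of which stand:

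- The chance of at least one positive primary finding is the same under both rules, and the gain almost vanishes if only one association is real.
- A fixed level lets each question be judged alone. Under Holm, whether the prospective result counts can depend on the cross-sectional one.
- The error for a single true null can rise from 2.5% towards 5%. This matters for the prospective hypothesis, which has the clearer time ordering, because the Implications section would read a positive association as possibly reflecting a physiological mechanism.

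The usual practical reason for the single-step rule is that it comes with simple matching 97.5% intervals. That carries less weight here, because the plan reports 95% intervals. The similarity of the hypotheses, which is the reason given, justifies correcting for two tests but does not favour Bonferroni over Holm.

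**Conclusion.** The point holds as an optional improvement, not as a correction. Within the plan's own .05 criterion, Holm never does worse on rejection and adds about 7 to 8 points of prospective power and 3 to 4 points of cross-sectional power at an OR of 1.25 in both analyses.

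The size rests on the Table 5 numbers, equal true ORs and a between-test correlation of 0 to 0.3; the last two are assumptions. It shrinks at large ORs and is close to zero if only one association exists. Absolute power falls under both rules if the prospective sample is below 1850 participants. That does not affect the validity of either procedure.

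**What to change.** In Criteria for Statistical Significance, before the blood pressure and drug-use data are analysed, replace the Bonferroni sentence with Holm's rule: test the smaller of the two primary P values at .025 and, if it is rejected, test the other at .05. Report Holm-adjusted P values against .05, that is, twice the smaller P, and for the other the larger of that value and its own P. State that Figures 1 and 2, calculated at .025, are then lower bounds on power for the sample sizes they assume.

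The cost is one or two sentences and no extra data or modelling. The price is that one decision depends on the other test, simple matching simultaneous intervals are lost (the plan does not use them), and the error for a single true null can approach .05. If the authors prefer to keep the two decisions independent, a sentence saying so would be a reasonable alternative.

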### Primary Statistical Analyses

Logistic regression will be used to estimate the odds of becoming a case from examination n to n+1 as a function of heavy occupational lifting. For the cross-sectional analysis, there will be a possibility of 3 observations per participant, 1 from each examination. For the prospective analysis, there will be a possibility of 2 observations per participant, 1 from the third to the fourth examination and one from the fourth to the fifth examination. The cross-sectional analysis will be controlled for sex, age, BMI, smoking, and education. The prospective analysis will, in addition to the variables of the cross-sectional analysis, be controlled for self-rated cardiorespiratory fitness, vital exhaustion, and BP at baseline. Self-rated cardiorespiratory fitness and vital exhaustion will only be included as covariates in the prospective analysis where the main point of interest is new cases and not prevalent cases as in the cross-sectional analysis. Generalized estimating equations will be used to estimate the parameters. Observations from the same person will be treated as repeated measurements. A first order autoregressive correlation structure is assumed. Should the estimated covariance matrix fail to converge, then we will resort to a variance component correlation structure.

The significance test will be based on the empirical SE and the Wald Statistic. The odds ratio (OR) between the exposed and the nonexposed will be calculated and presented with a 95% CI. The CI will be based on the empiric SE.

### Statistical Power

The power calculations are based on, inter alia, the following assumptions:

In total, 20% of the participants were hypertensive at baseline [16].In total, 15.68% (1830/11,670) participants performed heavy occupational lifting at baseline (Table 2).In total, 55% of the participants who were normotensive at examination n would meet the case criteria (antihypertensive drug usage or an above median delta of SBP) at examination n+1.The intraperson correlation coefficient equals .5 in the cross-sectional analysis and .1 in the prospective analysis.

Table 5 shows the expected numbers of observations, participants, and “cases” that will be included in the primary analyses. It also shows the variance inflation factor, which is a function of the assumed intraperson correlation and the mean numbers of observations per participant.

**Table 5 table5:** Number of observations, participants, and estimated cases that we expect to include in the primary analyses.

Analysis	Number of observations	Number of participants	Observations/Participants	Estimated number of cases^a^	Variance inflation factor
Cross-sectional	11,670	7166	1.63	2334	1.31
Prospective	4746	3271	1.45	2610	1.05

^a^A case in the primary analysis will be defined as the shift from no use of antihypertensive drugs in examination n to use of antihypertensive drugs in examination n+1 or an above median delta value of systolic blood pressure (systolic blood pressure in examination n+1-systolic blood pressure in examination n).

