### Assessment of Exposure

In all 3 examinations, the self-reported information on level of OPA was obtained by asking the question: “Please describe your level of OPA within the past year” with the following response categories: “(1) predominantly sedentary; (2) sitting or standing, some walking; (3) walking, some handling of material; (4) heavy manual work.” If answering 3 or 4, an additional question regarding heavy occupational lifting was applied. The question was: “Do you lift heavy burdens?” with the response categories: “(1) yes and (2) no.” Participants will be classified as exposed to heavy occupational lifting by answering “yes” to the question concerning heavy burdens, and those participants answering 1, 2, and 3 or 4 in combination with not lifting heavy burdens will be classified as the reference group.

Between the examinations of data collection, we do not have any information about their exposure to OPA or lifting. However, for the prospective analysis, a measure of the stability of exposure was accounted for by cross-tabulating the self-reported exposure at examination 3 by exposure at examination 4 and also the self-reported exposure at examination 4 by exposure at examination 5. Among those participants responding to the self-reported exposure to OPA at examinations 3 and 4, 13.4% (329/2459) stated to be exposed to heavy lifting in examination 3 and 12.0% (295/2459) in examination 4. Among those participants responding to the self-reported exposure to OPA at examinations 4 and 5, 8.29% (146/1762) stated to be exposed to heavy lifting in examination 4 and 6.81% (120/1762) in examination 5. An evaluation of the agreement (Cohen kappa) between exposure to heavy occupational lifting in examinations 3 and 4 was .30, and the agreement between exposure to heavy occupational lifting in examinations 4 and 5 was .40, indicating a fair agreement between exposure to heavy occupational lifting across examinations (see Tables 1-4) [12].

**Table 1 table1:** Number of participants who responded to the questions on level of occupational physical activity (OPA) at examinations 3 and 4.

Examination 3 (1991-1994)	Examination 4 (2001-2003)			
	1^a^	2	3	4
1	599	223	45	9
2	173	511	123	8
3	57	210	367	34
4	3	21	26	50

^a^1=predominantly sedentary; 2=sitting or standing, some walking; 3=walking, some handling of material; 4=heavy manual work.

**Table 2 table2:** Number of participants who reported to have heavy occupational lifting at examinations 3 and 4.

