### Differences in the Study Population

Smaller numerical differences were observed between the participants answering on the level of OPA and the attending participants.

Cross-sectionally, the participants responding to the level of OPA were 9.8 years younger (mean age 49.0 years among the participants answering on the level of OPA and 58.8 years among the attending), had a higher level of education than the attending participants (13.87% [1619/11,670] participants responding to the level of OPA were noneducated and 20.69% [4328/20,922] among the attending), and a higher proportion of the participants responding to the level of OPA stated to be exposed to heavy occupational lifting (14.04% [1638/11,670] among the participants responding to the level of OPA and 8.48% [1774/20,922] among the attending participants).

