**Occupational physical activity**				
	Predominantly sedentary		4407 (37.8)	
	Sitting or standing, some walking		4079 (35.0)	
	Walking, some handling of material		2729 (23.4)	
	Heavy manual work		455 (3.9)	
Occupational heavy lifting (% yes)			1830 (15.7)	
Vital exhaustion (sum, 0-17)		3.0 (3.5)		0-17
Cardiorespiratory fitness (% similar level as peers)			6390 (54.8)	
Observation per participant		2.0 (0.8)		1-3

Prospectively, the participants answering on the level of OPA were 11.0 years younger (mean age 48.0 years among participants responding to the level of OPA and 59.0 years among the attending). The smokers were 2.31 percentage points higher (38.96% [2311/5932] of the participants responding to the level of OPA were current smokers and 36.65% [6930/18,908] among the attending); they had a higher level of education than the attending participants (12.39% [735/5932] of the participants responding to the level of OPA were noneducated and 19.76% [3737/18,908] among the attending). A higher proportion of the participants responding to the level of OPA stated to be exposed to heavy occupational lifting (17.52% [1039/5932] among the participants responding to the level of OPA and 8.34% [1576/18,908] among the attending participants), and a higher proportion of the participants responding to the level of OPA stated to have a level of cardiorespiratory fitness similar to their peers (57.67% [3421/5932] among the participants responding to the level of OPA and 45.57% [8617/18,908] among the attending).

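### The heavy-lifting counts contradict each other (1830, 1638, 1774), and the exposure-stability figures do not follow the protocol's own exposure rule

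*Protocol article*

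**What the plan says.** **Exposure rule (Methods, Assessment of Exposure).** Occupational physical activity (OPA) has four levels, and the lifting question is put only to people at level 3 or 4. A yes means exposed. For everyone else: "those participants answering 1, 2, and 3 or 4 in combination with not lifting heavy burdens will be classified as the reference group". OPA 1-2 is therefore unexposed by definition.

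**Exposed count.**
- Statistical Power: "In total, 15.68% (1830/11,670) participants performed heavy occupational lifting at baseline (Table 2"). Table 7 also has 1830 (15.7%).
- Results, Differences in the Study Population, cross-sectional paragraph: "14.04% [1638/11,670] among the participants responding to the level of OPA and 8.48% [1774/20,922] among the attending participants".
- Same section, prospective paragraph, and Table 8: "17.52% [1039/5932] among the participants responding to the level of OPA".

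**Stability.** Assessment of Exposure reports, for people who answered the OPA question at both examinations, "13.4% (329/2459) stated to be exposed to heavy lifting in examination 3 and 12.0% (295/2459) in examination 4". For examinations 4 and 5 it gives 146/1762 (8.29%) and 120/1762 (6.81%). The kappas are .30 and .40, summarised as "indicating a fair agreement between exposure to heavy occupational lifting across examinations", with reference to Tables 1-4.

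**The concern.** Two counts are given for one quantity on one denominator, and one of them exceeds the count for the larger group that contains it. At least one printed figure is wrong, and one of the candidates is the exposure share in the power calculation.

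The stability figures raise a different problem. Their numerators appear to come from people in manual work at both examinations, and their denominators from everyone. Someone who lifted at examination 3 and had a desk job at examination 4 is, by the protocol's rule, exposed and then unexposed. That is the kind of change a stability analysis exists to show, and the tables have no place for it. The article says it has no exposure information between examinations, so these tables are its only evidence on how well one baseline answer represents about ten years.

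**Working it through.** **1. The denominators agree.** From Flow of Participants: (10,135 − 5031) + (6237 − 2600) + (4550 − 1621) = 11,670 responding observations, and 10,135 + 6237 + 4550 = 20,922 attending. The 11,670 are a subset of the 20,922.

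**2. The counts do not.** 1830/11,670 = 15.68%, 1638/11,670 = 14.04% and 1774/20,922 = 8.48%. Each percentage is right for its own count, so rounding is not the cause. 1830 and 1638 cannot both be right, and 1830 in the subset cannot exceed 1774 in the whole. Table 7 has 2729 + 455 = 3184 observations in OPA 3-4. 1830 would be 57.5% of these and 1638 would be 51.4%; neither is impossible, so this does not decide between them.

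**3. Effect on power.** Table 5 reproduces: 0.20 × 11,670 = 2334 and 0.55 × 4746 = 2610 cases; variance inflation 1 + (1.63 − 1) × 0.5 = 1.31 and 1 + (1.45 − 1) × 0.1 = 1.05. The power curves are in figures not shown, so I recomputed power as Φ(ln OR / SE − z), with z for two-sided 0.025 and SE² = VIF × [1/(n₁p₁(1−p₁)) + 1/(n₀p₀(1−p₀))]. Here p₀ and p₁ are set so that the overall case share is 20% or 55%. The odds ratio of 1.25 is my illustration.

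| Analysis | Exposed share | Power at OR 1.25 | OR for 80% power |
|---|---|---|---|
| Cross-sectional | 15.68% | 83% | 1.24 |
| Cross-sectional | 14.04% | 79% | 1.25 |
| Prospective | 15.68% | 67% | 1.29 |
| Prospective | 14.04% | 63% | 1.31 |
| Prospective | 17.52% (Table 8) | 71% | 1.28 |

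**4. Who is in Tables 2 and 4.**

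| | Exam 3 to 4 | Exam 4 to 5 |
|---|---|---|
| All responders (Tables 1, 3) | 2459 | 1762 |
| OPA 3-4 at both | 367+34+26+50 = 477 | 219+13+13+22 = 267 |
| Total of lifting table (Tables 2, 4) | 236+93+59+90 = 478 | 94+52+26+95 = 267 |
| Left OPA 3-4 | 57+210+3+21 = 291 | 43+112+7+13 = 175 |
| Entered OPA 3-4 | 45+9+123+8 = 185 | 30+1+73+3 = 107 |
| OPA 1-2 at both | 1506 | 1213 |

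Apart from one person in Table 2, the lifting tables are the blocks for OPA 3-4 at both examinations. The numerators 329, 295, 146 and 120 are their margins. Leavers and entrants are in the denominator but can never count as exposed.

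**5. Bounds under the stated rule.** The extremes are that none or all of the leavers lifted at the earlier examination, and none or all of the entrants at the later one.

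| | Exam 3 to 4 | Exam 4 to 5 |
|---|---|---|
| Exposed, earlier exam | 329/2459 = 13.4% to 620/2459 = 25.2% | 146/1762 = 8.3% to 321/1762 = 18.2% |
| Exposed, later exam | 295/2459 = 12.0% to 480/2459 = 19.5% | 120/1762 = 6.8% to 227/1762 = 12.9% |
| Still exposed, of those exposed earlier | 236/620 = 38% to 236/329 = 72% | 94/321 = 29% to 94/146 = 64% |
| Kappa, full sample | .27 to .72 | .23 to .68 |

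**6. Kappa as printed.** Table 2: observed agreement .682, chance .544, kappa (.682 − .544)/(1 − .544) = .30, as stated. Table 4: .708 and .495 give .42, not .40.

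**7. Were any leavers lifters?** Table 8 has 1497 + 234 = 1731 observations in OPA 3-4 and 1039 lifters, hence 692 non-lifters. If no leaver had lifted, the pairs alone would contain 149 + 121 + 291 + 175 = 736 non-lifters. At least 736 − 692 = 44 of the 466 leavers therefore lifted, assuming the pairs lie within Table 8's 5932 observations. The pooled baseline share from the stability text, (329 + 146)/(2459 + 1762) = 11.3%, is also well below Table 8's 17.5%.

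**The case against.** **The power input may be right.** A reader might infer that 15.68% is the error. The article does not support that: 1830 agrees with Table 7, and the faulty figures may be 1638 and 1774, which share one sentence. The effect on power is also modest and, with Table 8's share, goes the other way for the prospective analysis. The data come from examinations already held, so no recruitment target depends on the share. All of this stands.

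**The reported stability may not be overstated.** The article never states a persistence figure; 72% and 64% are only what can be read from its tables. It reports kappa, and adding the large group in OPA 1-2 at both examinations can raise kappa. If 40% to 69% of both leavers and entrants lifted (an assumption), kappa is .50 to .38 for examinations 3-4, above the printed .30, and .44 to .32 for examinations 4-5, around the printed .40. So the inference that agreement is overstated fails. What remains is that the printed kappas describe a selected subgroup, not the study's exposure variable.

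**The bounds are wide.** The Table 8 check requires only 44 of 466 leavers to be lifters, about 9%. At that rate the examination 3 share would be about 14.5% and persistence about 66%, close to the printed tables. This is fair: the direction for shares and persistence is fixed, the size is not.

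**A null would not be over-read.** One might fear that a null would be presented as evidence of no effect. Implications of the Proposed Analysis says instead that a null would call for further study in populations with wider exposure. That fear is not borne out by the text.

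**Conclusion.** The point holds as a contradiction in printed figures and a departure from the stated exposure rule. The counts 1830, 1638 and 1774 cannot stand together; the article does not show which is wrong, and the power section cites a table that does not hold its figure. If 1638 is right, cross-sectional power at an odds ratio of 1.25 loses about 4 points. That rests on Table 5's observations, case shares and variance inflation, and on a Wald approximation, since the article's own curves could not be checked.

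The four stability shares are lower bounds and the readable persistence is an upper bound. The Table 8 check indicates that the limiting case of no lifters among leavers does not hold in both pairs. Kappa under the study's definition is unknown in either direction. No outcome, model or significance level is affected, but the figures describe the exposure on which both primary analyses rest, so they should be corrected.

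**What to change.** 1. Recount exposed observations once under the rule in Assessment of Exposure. Use that count in Statistical Power, Differences in the Study Population and Table 7, and reconcile the count for all attending observations with it.
2. Correct the reference to Table 2 in Statistical Power; the figure is in Table 7.
3. Rebuild Tables 2 and 4 on all 2459 and 1762 people, with OPA 1-2 coded unexposed. Resolve the one-person difference (478 against 477).
4. Restate the exposed shares and kappa from the rebuilt tables, and add the share of exposed people still exposed at the next examination. If the restricted tables are kept as well, label them as OPA 3-4 at both examinations and correct Table 4's kappa to .42.
5. Base the prospective power curve on the prospective population's own share. Redraw either curve only where the reconciled or population-specific share differs from 15.68%.

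The cost is re-tabulation of OPA and lifting answers already held; Flow of Participants lists only blood pressure and drug data as still to come. Some stated figures may become less favourable.

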**Results:**

In the third examination in 1991-1994, 10,135 out of 16,560 participants attended (61.20%), in the fourth examination in 2001-2003, 6237 out of 12,599 participants attended (49.50%), and in the fifth examination in 2011-2015, 4550 out of 9765 participants attended (46.59%). On the basis of the inclusion criteria of answering to the level of occupational physical activity, 5031 observations were excluded from examination 3, 2600 from examination 4, and 1621 from examination 5. Hence, the final populations for the cross-sectional and prospective analysis are assumed to include less than 7166 participants in the cross-sectional analysis and less than 1850 participants in the prospective analysis due to the additional inclusion criteria of measured BP and use of antihypertensive drugs.

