## Results

### Flow of Participants

In the third examination in 1991-1994, 10,135 out of 16,560 (61.20%) participants attended; in the fourth examination in 2001-2003, 6237 out of 12,599 (49.50%) participants attended; and in the fifth examination in 2011-2015, 4550 out of 9765 (46.59%) participants attended. On the basis of the inclusion criteria of responding to the level of OPA, 5031 observations were excluded from examination 3; 2600 from examination 4; and 1621 from examination 5. Hence, the final populations for the cross-sectional and prospective analysis are assumed to include less than 7166 participants in the cross-sectional analysis and less than 1850 participants in the prospective analysis (Figure 3), due to the additional inclusion criteria of measured BP and use of antihypertensive drugs. The information on BP and use of antihypertensive drugs will be provided after submission of this protocol paper.

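### The prospective primary analysis has two incompatible sample sizes: 3271 participants (4746 observations) in Table 5, and fewer than 1850 participants in the abstract and Results

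*Protocol article*

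**What the plan says.** The Statistical Power section presents Table 5 as the "Number of observations, participants, and estimated cases that we expect to include in the primary analyses". Its prospective row reads "Prospective 4746 3271 1.45 2610 1.05": observations, participants, observations per participant, cases and variance inflation factor (VIF). The same section then says "The statistical powers of the primary hypotheses are given in Figures 1 and 2", and bases the calculations on the listed assumptions and "a two-tailed significance level at *P*=.025, for each of the two hypotheses".

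The abstract gives another size for the final prospective population: "less than 1850 participants in the prospective analysis due to the additional inclusion criteria of measured BP and use of antihypertensive drugs". Flow of Participants in the Results repeats it as "less than 1850 participants in the prospective analysis (Figure 3" and points to Figure 3.

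Table 8 gives the starting point: 5932 observations on 4089 participants who answered the question on occupational physical activity (OPA). Primary Statistical Analyses allows each participant up to two prospective observations. Inclusion Criteria requires normotension at examination n, and blood pressure and drug-use data at both n and n+1.

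**The concern.** Both figures describe the population of the same primary analysis, and neither is qualified in a way that lets them coexist. Table 5 is not a count taken before exclusions, because it already leaves out the assumed hypertensives. Going from 3271 to under 1850 would need a further loss of about 43% (1 − 1850/3271 = 0.43), and no such loss is assumed anywhere.

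The prospective hypothesis is one of two primary hypotheses, each tested at .025. Methodological Challenges says that the SBP-case outcome was chosen because power for hypertension as a yes/no outcome would be insufficient, so expected prospective power shaped the choice of outcome. The Discussion also says how a null finding would be read. How informative a null would be depends on which count is right.

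**Working it through.** **Inputs.** Table 8: 5932 observations, 4089 participants. Statistical Power: 20% hypertensive at baseline, 55% cases among normotensives, 15.68% exposed, intraperson correlation .1 for the prospective analysis. Level: .025 two-sided (z = 2.241). The text gives no single target odds ratio (OR) or power, and Figure 2 is not shown. OR 1.3 is used here as an illustration.

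**Step 1: reproduce the prospective row of Table 5.**
- Observations: 0.80 × 5932 = 4745.6, printed as 4746.
- Participants: 0.80 × 4089 = 3271.2, printed as 3271.
- Observations per participant: 4746 / 3271 = 1.45.
- Cases: 0.55 × 4746 = 2610.
- VIF: 1 + (1.45 − 1) × 0.1 = 1.045, printed as 1.05.

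The whole row follows from Table 8 and the stated assumptions. Nothing is taken off for missing blood pressure or drug-use answers.

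**Step 2: test the two counts against each other.** At two observations each, 1850 participants give 2 × 1850 = 3700 observations, which is below 4746. The counts cannot both hold.

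**Step 3: look for a source of the 1850.**
- With at most two observations each, the number of participants who have two is 5932 − 4089 = 1843, close to 1850.
- Assessment of Exposure reports 2459 people who answered the OPA question at both examinations 3 and 4. Less 20%, that is 0.80 × 2459 = 1967. This already exceeds 1850, before adding anyone who contributes only the later interval and before removing anyone for missing data.
- In the same sentence, the cross-sectional limit of 7166 equals the full count of OPA responders in Table 7. The parallel prospective limit would be 4089.

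**Step 4: power under each count.** Wald test on the log OR:

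SE² = VIF × [1/(n·e·p1(1−p1)) + 1/(n·(1−e)·p0(1−p0))], power = Φ(ln OR / SE − 2.241)

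Here n is the number of observations and e = 0.1568; p0 and p1 are the case proportions in unexposed and exposed, set so that the overall proportion is 0.55. At OR 1.3, p0 = 0.540 and p1 = 0.604.

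For Table 5, n/VIF = 4746/1.045 = 4542, SE = 0.0832, ln 1.3 / SE = 0.2624/0.0832 = 3.15, and power = Φ(0.91) = 82%.

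| Count | Observations | VIF | Power at OR 1.3 | OR for 80% power |
|---|---|---|---|---|
| Table 5 as printed | 4746 | 1.045 | 82% | 1.29 |
| 1850 at 1.45 each | 2683 | 1.045 | 55% | 1.41 |
| 1850 at one each | 1850 | 1.00 | 41% | 1.50 |
| 1850 at two each | 3700 | 1.10 | 68% | 1.35 |

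The VIF rises to 1.10 in the last row because it depends on the mean number of observations per participant: 1 + (2 − 1) × 0.1. A comparison of two proportions gives powers within one percentage point of these.

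**The case against.** The strongest reply is that Table 5 is the sound side and the 1850 a slip in the text. Table 5 reproduces to the unit; the 1850 is derived nowhere in the readable text, sits next to 1843, and is hard to reach under the document's own assumptions (1967 from one interval alone). If so, the abstract and Results need correcting, and Table 5 and Figure 2 stand on this point. That argument has weight. A reader might infer from the contradiction that Table 5 and Figure 2 are wrong, or that prospective power is heavily overstated, and the documents do not support either inference. Nor do they prove the opposite: Figure 3, to which the Results tie the figure, is not shown, and the match with 1843 is only an inference.

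It can also be said that the data are already collected, that blood pressure and drug data were still to come, that no target power is promised, and that the OR will carry a confidence interval. All true, and this makes the matter one of correction rather than of failed design. It does not remove the contradiction.

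One could go further and take another 20% off 1850 for baseline hypertension. The Results call these the final populations, although the parallel 7166 is a count before exclusions. That case is a conditional extreme, not an established consequence.

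**Conclusion.** The contradiction is established: both figures describe the same primary analysis, and no readable text reconciles them. Which one is wrong is not established. Even if Table 5 is the correct side, 3271 is an upper limit under the 20% assumption, since the Results expect the blood pressure and drug-use criteria to reduce the numbers and Table 5 makes no allowance for that.

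The loss of power applies only if the limit of 1850 is right. Power at OR 1.3 would then be about 55% instead of about 82%, and the OR detectable with 80% power about 1.41 instead of about 1.29. These figures treat 1850 as reached, so they are best cases for each assumed number of observations per participant. They rest on the plan's exposure, case and correlation assumptions, on an unadjusted comparison, and on reading Figure 2 as drawn from the Table 5 counts. That is the natural reading but cannot be checked.

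**What to change.** Derive the prospective count once under all the stated criteria: OPA answer at n, normotensive at n, and blood pressure and drug-use answers at n and n+1. Use that count in the abstract, Flow of Participants, Figure 3 and Table 5.

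- If the limit of 1850 is the error, correct the abstract and Results. Either allow for missing data in Table 5 or label 3271 an upper limit.
- If it is right, recompute the prospective row of Table 5 (observations, cases, VIF), redraw Figure 2, and state the OR detectable with 80% power.

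The cost is text, one table row and at most two figures. No new participants, data or change of design are needed. The downside is that the stated power may become less favourable.
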